### 2.6. Outcomes

#### 2.6.1. Bone Mineral Density Measurements

The primary outcome is the change in cortical and trabecular vBMD as measured by high resolution peripheral quantitative computed tomography (HR-pQCT, Xtreme CT; Scanco Medical, Brüttisellen Switzerland) at the distal tibia and distal radius after 12 months of intervention compared to placebo. Participants will be scanned at baseline (Time point: 0) and 12 months (Time point: 12 month) to assess changes.

Scans will be performed by a trained researcher in HR-pQCT scanning and interpretation, according to the established guidelines and manufacturer’s instructions [29]. Briefly, this involves the upper and lower limbs being positioned in anatomically formed carbon fibre casts provided by the manufacturer (to minimize limb motion during scanning). Once the limb is placed into the gantry of the scanner, a 2D scout view is obtained to select the region of interest for the 3D measurement. Using the fixed offset method, which is suitable for follow-up studies, the operator will place a reference line at the inflection point on the endplate of the distal radius or tibial plafond. The scan region begins 9.5 mm and 22.5 mm proximal to the reference line for the radius and tibia, respectively. The HR-pQCT images will be analysed with specific software developed by the manufactures. A semi-automated slice-by-slice contouring process will be utilized to identify the periosteal boundary of the bone, thereby extracting the bone region from the surrounding soft tissue. The delineation of the cortical and trabecular compartments will then be performed automatically using a filter and threshold-based algorithm.

Additional bone mineral density measures include changes in aBMD measured by a trained DEXA researcher at the following sites: spine (L1–L4), total hip, femoral neck, and forearm, using a Hologic DXA machine (Time points: 0, 6, and 12 months). Following the manufacturer’s and standard guidelines, the non-dominant hip and forearm will be assessed using DXA. In the presence of disorders such as fragility fractures in the non-dominant site, the opposite site will be scanned. All scans will be analysed by one person to minimize intra-operator errors. A study that will assess the coefficient of variation in DXA measurements will be performed using 30 participants scanned twice. Calcaneal (heel) measurements will be carried out using quantitative ultrasound (QUS, Achilles, Abingdon, UK) and measured at time points: 0, 6, and 12 months.

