### 2.7. Sample Size

The sample size calculation was based on the changes observed in total tibia volumetric BMD (vBMD) between the two treatment arms (statistical power 80%, probability of type I error 0.05) and is adequate to achieve a difference of 1% (standard deviation 1.78%) in a previously published study [21]. This estimation showed the need to recruit 50 study participants per treatment arm. Expecting a drop-out rate of 20% from baseline to follow-up measurements, an additional sample of 24 study participants will be recruited, thus leading to total sample size of 124 (i.e., 62 per treatment arm).

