### 2.8. Statistical Analysis

All continuous variables will be checked for the normality of their distribution. Normally distributed variables will be presented as Mean (standard deviation), while non-normally distributed ones will be presented as Median (interquartile range). General linear models (Repeated Measures Analysis of Variance) will be used to examine within-group changes in the majority of primary and secondary outcome measures across all time points (baseline, 6-, and 12-month follow-up) separately for each group (probiotic and placebo), as well as between-group differences at each time point. Within-group changes across all time points (baseline, versus post-intervention, versus follow-up) and between-group differences in each time-point will be also examined for biological sample data using the same statistical test. Appropriate corrections will be applied for post hoc multiple comparisons, while all analyses will be adjusted for potential confounding factors (e.g., age, body mass index, sunlight exposure, etc.). Correlations will also be used to explore the relationship between questionnaires and biological sample data.

Mediation analysis will also be conducted to examine the potential mediating role of changes in gut microbiota composition, and to examine the potential mediating role of other biological markers on the changes observed in BMD and bone metabolism indices. This will be based on a multiple regression model between the intervention, the outcome, and the potential mediators (e.g., a one of the mediation tests will assess the effect of the intervention on vBMD, examining the changes in serum concentrations of inflammatory markers as potential mediators of the intervention’s effect). The analysis will provide a % mediating effect, i.e., the % of the variability of the examined outcome explained by the examined mediating factors.

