All statistical analyses will be performed using the SPSS statistical analysis software version 29 for Windows. Both Per-Protocol (PP), and Intention-to-Treat (ITT) analyses will take place. Per-protocol analysis will compare treatment groups, including only those study participants who completed the treatment that was originally allocated to them. Adherence to the intervention will also be taken into consideration in the per-protocol analysis by identifying and excluding potential non-adherent study participants from the analysis. All reported *p*-values will be two-tailed, while the level of statistical significance will be set at *p* < 0.05.

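### Four primary vBMD measures are each judged at p < 0.05, with correction promised only for post hoc comparisons and a sample size built on one test of a fifth measure

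*Protocol article*

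**What the plan says.** Section 2.6.1 opens: "The primary outcome is the change in cortical and trabecular vBMD". It places the measurement "at the distal tibia and distal radius after 12 months of intervention compared to placebo". Two compartments at two sites make four measures under the single label of primary outcome. The section does not order them, combine them, or say how many must succeed.

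Section 2.8 sets one threshold for everything: "All reported *p*-values will be two-tailed, while the level of statistical significance will be set at *p* < 0.05". On multiplicity it says "Appropriate corrections will be applied for post hoc multiple comparisons". On analysis sets it says "Both Per-Protocol (PP), and Intention-to-Treat (ITT) analyses will take place", and it names neither as the main one.

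Section 2.7 bases the sample size on "total tibia volumetric BMD (vBMD) between the two treatment arms (statistical power 80%, probability of type I error 0.05" and calls it "adequate to achieve a difference of 1% (standard deviation 1.78%) in a previously published study". The result is 50 evaluable per arm, raised to 62 per arm (124 in total) for 20% dropout. Total tibia vBMD is not among the four measures of Section 2.6.1.

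**The concern.** The sample size assumes one test at 0.05, while the outcome definition supplies four. The correction promised in Section 2.8 is worded for post hoc comparisons, and the four measures are pre-specified primary ones, so on its plain wording it does not reach them.

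If the trial finds a difference in one compartment at one site and nothing in the other three, the plan gives no basis for saying whether its primary objective was met. A claim resting on that one result would not carry the stated 0.05 error rate. The stated 80% power also belongs to a measure that the outcome definition does not list.

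**Working it through.** **Inputs.** Four primary measures (Section 2.6.1). Two-sided 0.05 for each test, and two analysis sets (Section 2.8). Difference 1%, SD 1.78%, power 80%, 50 evaluable per arm, dropout 20% (Section 2.7). The correlation between measures and the share of patients in the PP set are not given. Both are assumed below and shown as ranges.

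**Step 1: the plan's own figure.** n per arm = 2 × (1.960 + 0.842)² × 1.78² / 1² = 49.7, so 50. Power at 50 is 80.2% by the normal approximation (79.4% by the t-test). For dropout, 100 / 0.8 = 125 against the stated 124, a trivial difference. The sample size reproduces, but for one test at 0.05.

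**Step 2: four measures in one analysis set, no true effect.** With independent measures, P(at least one p < 0.05) = 1 − 0.95⁴ = 0.185. With correlated measures, the probability that any of four equally correlated z-statistics exceeds 1.96 in absolute value was simulated with 1,000,000 draws:

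| Assumed correlation | P(at least one) | Multiple of 0.05 |
|---|---|---|
| 0 | 18.5% | 3.7 |
| 0.3 | 17.4% | 3.5 |
| 0.5 | 15.6% | 3.1 |
| 0.7 | 13.1% | 2.6 |
| 0.9 | 9.4% | 1.9 |

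**Step 3: two analysis sets.** PP is taken as a subset holding 80% to 95% of patients, so the ITT and PP statistics correlate at the square root of that share. On one measure, allowing either set to support a claim gives 6.0% (PP share 95%) to 7.1% (80%). With four measures at correlation 0.5, the 15.6% becomes 18.5% to 21.4%. The four measures add about 10.6 points to the nominal 5%, and the choice of set adds a further 2.9 to 5.8.

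**Step 4: what correction would cost.** Both Bonferroni and the first Holm step use 0.05 / 4 = 0.0125, with critical value 2.498.

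- Independent measures each tested at 0.0125: 1 − 0.9875⁴ = 0.049.
- Power per measure at 50 per arm: 1 / (1.78 × √(2/50)) = 2.809, and Φ(2.809 − 2.498) = 0.62.
- n for 80% power at 0.0125: 2 × (2.498 + 0.842)² × 1.78² = 70.7, so 71 evaluable per arm. Allowing for dropout, 71 / 0.8 = 88.75, so 89 recruited per arm.

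Step 4 assumes that the 1% and 1.78% apply to each of the four measures. Section 2.7 states them for total tibia vBMD only.

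**The case against.** The strongest reply is that this is a journal article. An analysis plan that is not shown may order the endpoints, state the success rule and name the confirmatory set; Section 4 itself refers to an a priori analysis plan. That stands for silence alone, and it leaves the ITT/PP part weak, since Section 2.8 says only that both analyses will be done. It does not answer what the article does state: a four-part primary outcome, one threshold for all p-values, correction worded for post hoc comparisons, and sizing for one test on another measure.

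A second reply is that the correction sentence is loose. HR-pQCT has only two time points and there are two arms, so that sentence has little pairwise testing to correct for the primary outcome and might be meant more widely; adjusted p-values can also be compared with 0.05. This is possible. But if correction across the four is intended, the 80% power in Section 2.7 is not the power of the corrected tests (Step 4).

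Third, success might require all four measures, and then there is no inflation. The article does not say so. Under that rule the stated power would not hold either: at 80% per measure, joint power would be 0.8⁴ = 41% if the measures were independent, and would reach 80% only if they moved together perfectly.

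Three stronger readings are tempting and are not supported:

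- That the error rate is about three times nominal. This needs both an any-one-counts rule and a moderate correlation, and the document gives neither.
- That a claim could rest on any of eight p-values. Nothing says a PP result alone may support one.
- That the mixed results of earlier trials show the effect of uncorrected testing across sites. Sections 1 and 4 attribute them to strains, durations, populations and low power, and do not say how those trials handled multiplicity.

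**Conclusion.** The concern holds in conditional form. As written, the plan does not hold 0.05 for a claim based on any one of the four primary measures. If any one may count, the family-wise rate in one analysis set is 9.4% to 18.5% over assumed correlations from 0.9 to 0. The lower end is still nearly double nominal. The ITT/PP choice is a secondary contributor.

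The mismatch between the sizing measure and the primary measures needs no such assumption: it is on the face of Sections 2.6.1 and 2.7.

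A positive result would not be uninterpretable. If all four p-values were reported, a reader could apply Bonferroni. The defect is that the plan leaves the meaning of success to be settled later and states a power figure for a different test.

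**What to change.** Amend before unblinding. Section 3 describes the study as ongoing and Section 2.5 keeps the blind until the analysis is complete, so the choice can be made without knowledge of results by group.

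1. Name ITT as the confirmatory analysis and PP as supportive.
2. Name one primary measure, tested at two-sided 0.05. Test the others only if it is significant, in a fixed order or by Holm.
3. Reconcile that measure with Section 2.7: either make total tibia vBMD the primary measure, or restate the power for the measure chosen, with its own difference and SD.
4. If all four stay primary, apply Holm at family-wise 0.05 in the ITT set and restate the power.
5. Say in Section 2.8 which comparisons the promised correction covers.

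Cost: with one named measure, the change is to wording and the 50 evaluable per arm stand, provided the 1% and 1.78% apply to that measure. The other measures lose stand-alone confirmatory status. Keeping all four costs more: power per measure at the first Holm step is about 62% with 50 evaluable per arm, and restoring 80% there would take 71 evaluable (89 recruited) per arm. That difference favours naming one measure.

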#### 2.6.2. Gut Microbiome Composition

Gut microbiome analysis will be performed on participant-collected stool samples. Participants will collect samples at home according to manufacturer’s instructions (Invitek, Berlin, Germany) prior to each study visit and return it to the lab for storage at −20 degrees centigrade. All samples will be analysed using 16S sequencing techniques using QIAGEN DNeasy Power Kit (Qiagen 12888, Hilden, Germany). Changes in profile, such as microbiome alpha diversity (richness, Shannon Diversity Index), phylogenic beta diversity, relative abundance of taxa, and functional potential from baseline to 12 months, will be investigated, and will also function as a compliance check for the intervention group to verify intake.

#### 2.6.3. Blood Biomarker Measurements

Blood samples will be drawn using standard sterile IV venipuncture techniques by a trained phlebotomist. All samples will be obtained from a vein in the antecubital fossa of the arm using standard phlebotomy procedures. Plasma and serum samples will be decanted and aliquoted into de-identifiable labelled tubes and stored in a −80 °C freezer for subsequent analysis. Serum and plasma will be processed, stored, and assayed in the La Trobe Nutrition Clinical Trial Laboratory. Deidentified samples will also be sent to accredited private pathology laboratories for further analyses for the measurement of the concentrations of blood biomarkers (Time points: 0, 6, and 12 months). The analyses of serum or plasma for all other biomarkers will be conducted after data collection is complete, using standardised procedures and assays. This includes bone formation (Procollagen type 1 N propeptide (P1NP), total and undercarboxylated osteocalcin) and blood–bone resorption (Serum type I collagen cross-linked C-Telopeptide (CTx) or Tartrate-resistant acid phosphatase 5b (TRAP 5b)); osteoclast differentiation molecules osteoprotegerin (OPG) and receptor activator of nuclear factor kappa-Β ligand (RANKL); calciotropic hormones 25-hydroxy vitamin D, 1,25-hydroxy vitamin D, parathyroid hormone (PTH), and calcitonin; renal and liver function markers to assess normal function; and inflammatory markers high sensitivity C-reaction protein (hsCRP) and interleukin-6 (IL-6).

#### 2.6.4. Dietary Intake

Dietary intake will be measured using 3-day food diaries at each time point, and analysed using FoodWorks 10 (Xyris software), the leading nutrition analysis software in Australia. Macro and micronutrient intake values will be derived from 3-day food diary analysis. Participants will be asked to record all food and drink intake for two weekdays and one weekend day that are typical of their usual diet. A validated food frequency questionnaire (FFQ), titled Comprehensive Nutrition Assessment Questionnaire [30], will also assess dietary intake and patterns, as well as fermentable carbohydrates at each timepoint. This FFQ was selected given its identification and quantification of fermentable carbohydrates (i.e., FODMAPs), known to impact gut microbiome composition [31].

#### 2.6.5. Body Composition and Anthropometry

Body composition will be measured using DXA (Hologic) by a trained researcher. Participants will attend all study visits fasted and at approximately the same time of day per timepoint to avoid variation. Body composition will also be measured using bioimpedance analysis (BIA) with the Tanita MC-780 analyser (Poznań, Poland). Body weight and standing height is measured by using a digital scale (Seca, Hamburg, Germany) with an accuracy of ±100 g and a commercial stadiometer (Leicester Height Measure; CMS Instruments, Oxford, UK) to the nearest 0.5 cm, respectively, while participants wear light clothing and no shoes.

#### 2.6.6. Self-Reported Questionnaires

Data collected through questionnaires will be self-reported, unless indicated where obtained with an interview with study participants. The questionnaires, administered via REDCap, will collect information on:

Demographics: The socio-demographic questionnaire will collect information on participants’ socio-demographic characteristics, i.e., date of birth, years of education, employment status, occupation, country of birth, marital status, ethnicity, and areas of residence (Time points: 0).

Medical History: Medical and surgical history will be obtained with an interview in order to verify that the eligibility criteria are met. Any medication used during the study (concomitant medications) will be recorded in the study diary/CRF. Concomitant medications will be coded according to the WHO Anatomic Therapeutic Chemical (ATC) classification system (Time points: 0).

Fracture Risk: The Fracture Risk Assessment Tool (FRAX^®^) (online version adopted to the Australian population) [32] will be used to calculate the 10-year probability of fracture without BMD. This calculation is based on age, weight, height, alcohol consumption, history of osteoporosis, and several other risk factors. FRAX^®^ was developed by the WHO, and is managed by the University of Sheffield in the UK. (https://www.sheffield.ac.uk/FRAX/tool.aspx, accessed on 1 July 2021) (Time points: 0).

Physical Activity: The Active Australia Questionnaire (AAQ) has an acceptable validity and reliability for recording physical activity levels in Australian middle-aged women [33]. Study participants will report the frequency and duration of time in the previous week spent walking briskly, in moderate-intensity leisure time physical activities, and in vigorous-intensity physical activities (Time points: 0, 6, and 12 months).

Sunlight Exposure: Data on sunlight exposure will be collected via the use of a validated questionnaire [34] that will record information on study participants’ personal ultraviolet B (UV-B) radiation exposure (i.e., time of day, latitude, and season) and modifying factors (i.e., cloud, tree cover, surface, clothing, and sunscreen use). Data on the dose of UV-B radiation in the areas of residence of study participants will also be extracted from the online records of the Australian Radiation Protection and Nuclear Safety Agency (Time points: 0, 6, and 12 months).

Participants will be instructed to report adverse events at the time of event. If it is determined that the intervention is not causative of the adverse event, the participant will be allowed to maintain their participation in the study. Further assessment of any adverse events will be examined as to whether these differ between intervention and control groups.

Table 1 below shows an overview of study data collection and time points.

### 2.7. Sample Size

The sample size calculation was based on the changes observed in total tibia volumetric BMD (vBMD) between the two treatment arms (statistical power 80%, probability of type I error 0.05) and is adequate to achieve a difference of 1% (standard deviation 1.78%) in a previously published study [21]. This estimation showed the need to recruit 50 study participants per treatment arm. Expecting a drop-out rate of 20% from baseline to follow-up measurements, an additional sample of 24 study participants will be recruited, thus leading to total sample size of 124 (i.e., 62 per treatment arm).

### 2.8. Statistical Analysis

All continuous variables will be checked for the normality of their distribution. Normally distributed variables will be presented as Mean (standard deviation), while non-normally distributed ones will be presented as Median (interquartile range). General linear models (Repeated Measures Analysis of Variance) will be used to examine within-group changes in the majority of primary and secondary outcome measures across all time points (baseline, 6-, and 12-month follow-up) separately for each group (probiotic and placebo), as well as between-group differences at each time point. Within-group changes across all time points (baseline, versus post-intervention, versus follow-up) and between-group differences in each time-point will be also examined for biological sample data using the same statistical test. Appropriate corrections will be applied for post hoc multiple comparisons, while all analyses will be adjusted for potential confounding factors (e.g., age, body mass index, sunlight exposure, etc.). Correlations will also be used to explore the relationship between questionnaires and biological sample data.

Mediation analysis will also be conducted to examine the potential mediating role of changes in gut microbiota composition, and to examine the potential mediating role of other biological markers on the changes observed in BMD and bone metabolism indices. This will be based on a multiple regression model between the intervention, the outcome, and the potential mediators (e.g., a one of the mediation tests will assess the effect of the intervention on vBMD, examining the changes in serum concentrations of inflammatory markers as potential mediators of the intervention’s effect). The analysis will provide a % mediating effect, i.e., the % of the variability of the examined outcome explained by the examined mediating factors.

All statistical analyses will be performed using the SPSS statistical analysis software version 29 for Windows. Both Per-Protocol (PP), and Intention-to-Treat (ITT) analyses will take place. Per-protocol analysis will compare treatment groups, including only those study participants who completed the treatment that was originally allocated to them. Adherence to the intervention will also be taken into consideration in the per-protocol analysis by identifying and excluding potential non-adherent study participants from the analysis. All reported *p*-values will be two-tailed, while the level of statistical significance will be set at *p* < 0.05.

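### The normality check in section 2.8 changes only how a skewed biomarker is displayed; no modelling scale or baseline adjustment is stated, which would cost power for strongly skewed markers

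*Protocol article*

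**What the plan says.** Section 2.8 of the protocol article starts with a normality check on all continuous variables. Its stated result is a choice of summary: mean and SD for normal variables, while "non-normally distributed ones will be presented as Median (interquartile range"). The section then names general linear models (repeated-measures ANOVA) for most primary and secondary outcomes. For the laboratory data, within-group changes and between-group differences at each time point "will be also examined for biological sample data using the same statistical test".

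All analyses are to be adjusted for potential confounders. The examples given are age, body mass index and sunlight exposure, in an open-ended list. The baseline value of the marker is not among them.

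Section 2.6.3 lists the blood markers, including "inflammatory markers high sensitivity C-reaction protein (hsCRP) and interleukin-6 (IL-6"). The abstract and section 1 make the biomarkers secondary outcomes, and section 1 includes lower inflammatory markers in the hypothesis. Section 2.8 uses inflammatory markers as its worked example of a mediator of the effect on vBMD.

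**The concern.** A distributional check is useful when it decides how the data are modelled. Here the plan looks for non-normality and attaches only a table format to it.

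If a marker fails the check and the text is followed as it stands, the reader sees medians and quartiles next to a p-value that compares arithmetic means. For a right-skewed concentration those are different quantities. The raw-scale comparison also depends heavily on a few high values, so it is less efficient when treatment acts proportionally.

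What is at stake is the mechanistic part of the trial: the secondary biomarker comparisons, and the mediation models that reuse the same variables. The article states no power for any biomarker, so it shows no margin for lost efficiency.

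**Working it through.** **The plan's own figure.** Section 2.7 works from "statistical power 80%, probability of type I error 0.05". The target difference of 1% and the SD of 1.78% are taken from an earlier trial. The normal-approximation formula gives

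n per arm = 2(1.96 + 0.8416)² × 1.78² / 1² = 2 × 7.849 × 3.168 = 49.7, so 50.

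This matches the 50 per arm that section 2.7 states. With 20% drop-out, 100 / 0.8 = 125, against a stated total of 124. The figure reproduces, but it concerns tibia vBMD. Only the 50 completers per arm are carried forward.

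**How far table and test diverge.** For a log-normal variable, mean / median = exp(σ²/2), where σ is the SD on the natural-log scale:
- σ = 0.3: exp(0.045) = 1.05
- σ = 0.5: exp(0.125) = 1.13
- σ = 0.8: exp(0.32) = 1.38
- σ = 1.0: exp(0.5) = 1.65

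**Inputs for power**
- From the article: 50 per arm (section 2.7) and two-sided testing at 0.05 (section 2.8).
- Assumed, because the article gives none of them: a log-normal marker, log-SD σ, baseline-to-12-month log correlation ρ of 0.5 to 0.7, and a multiplicative 30% reduction, so δ = −ln 0.7 = 0.357.

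**Log scale, closed form.** Power ≈ Φ(δ / (s√(2/50)) − 1.96), where s = σ√(2(1−ρ)) for the change test and s = σ√(1−ρ²) for ANCOVA. At σ = 1.0:
- Change, ρ = 0.5: s = 1.000, δ/(0.2s) = 1.78, power 43%.
- Change, ρ = 0.7: s = 0.775, δ/(0.2s) = 2.30, power 63%.
- ANCOVA, ρ = 0.5: s = 0.866, δ/(0.2s) = 2.06, power 54%.
- ANCOVA, ρ = 0.7: s = 0.714, δ/(0.2s) = 2.50, power 70%.

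**Raw scale, by simulation.** Baseline and 12-month values were generated as log-normal. Each data set was analysed four ways: raw or log scale, by change score or by ANCOVA. With two time points, the change-score t-test is the group-by-time test of the repeated-measures ANOVA. Approximate power, with the range running from ρ = 0.5 to ρ = 0.7:

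| log-SD | Change, raw | Change, log | ANCOVA, raw | ANCOVA, log |
|---|---|---|---|---|
| 0.8 | 36–53% | 60–81% | 55–69% | 71–87% |
| 1.0 | 23–32% | 43–64% | 34–45% | 54–70% |

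Repeat simulations agree to within about 2 percentage points, and the log-scale columns agree with the closed form.

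**Mild skew, same 30% effect.** At log-SD 0.3, power for the change test is essentially 100% on both scales. At log-SD 0.5 it is 83% raw against 94% log (ρ = 0.5), and 96% against 99.5% (ρ = 0.7). Part of this closeness is a ceiling, because a 30% effect is easy to detect at low variability. When the effect is instead sized for about 80% power in log-scale ANCOVA, the raw-scale loss is as follows:
- log-SD 0.3: 5–6 points for the change test, 2–3 for ANCOVA.
- log-SD 0.5: about 13 points for the change test, 5–6 for ANCOVA.

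**Scale and baseline adjustment separated.** At log-SD 1.0 and ρ = 0.7, the change of scale alone takes the change test from 32% to 64%, and ANCOVA from 45% to 70%. Baseline adjustment alone, on the raw scale, takes 32% to 45%. Comparing raw change directly with log ANCOVA (32% to 70%) would credit both gains to the transformation.

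**Type I error.** Under no effect, raw-scale rejection rates stay near or slightly below 5%, at about 4–6% across the scenarios.

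**The case against.** The strongest reply is that the article nowhere says the markers are analysed untransformed. It names a test, and a log-transformed marker can go through that same test. The article is a condensed account, and a fuller analysis plan that is not shown may fix the scale. This stands as far as it goes: a reader might infer that raw-scale analysis is settled, and the text does not support that. What remains is that section 2.8 addresses non-normality explicitly, states one consequence, which concerns display, and then assigns the test.

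Secondly, the article gives no distribution, SD, correlation or expected effect for any marker. Skew in hsCRP and IL-6 is an assumption, and section 2.2 excludes smokers, women with BMI above 32 kg/m² and those with inflammatory conditions, which could thin the upper tail. If the effect were additive on the raw scale, the log-scale gain could shrink or vanish. All of this stands, so the power figures are conditional.

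Thirdly, the simulation uses two time points without other covariates, whereas section 2.8 plans three time points for these markers, with adjustment. The figures therefore illustrate the loss and do not predict the trial's power.

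Finally, it is tempting to conclude that most of the listed biomarkers lose much of their power, or that the trial is likely to miss a real effect. Neither follows. The large losses need strong skew, and nothing in the article shows that P1NP, CTx, osteocalcin or the other markers are that skewed.

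**Conclusion.** The point holds in a limited form. As published, the plan detects non-normality but gives it no analytic consequence. It assigns the biomarkers to repeated-measures ANOVA with no stated transformation and no stated adjustment for the baseline value. For a strongly right-skewed marker (log-SD about 0.8 or more) with a proportional effect, the scale alone is worth roughly 20 to 32 percentage points on the change test and 16 to 25 on ANCOVA at log-SD 0.8 to 1.0, and the displayed and tested quantities differ. For mildly skewed markers the cost is small.

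The consequence is lost efficiency and harder interpretation, not false positives. It falls on secondary and mediator biomarkers; the vBMD primary outcome and its sample size are untouched. The size depends on assumed log-normality, log-SD, correlation and a multiplicative 30% effect. The article supplies only the 50 per arm and the two-sided 0.05 level.

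**What to change.** State, before the assay values are analysed, that:
- right-skewed blood biomarkers are log-transformed before modelling: at least hsCRP and IL-6, and any other marker whose model residuals are clearly skewed on blinded, pooled data;
- the between-arm comparison adjusts for the log baseline value;
- the result is reported as a ratio of geometric means with a 95% confidence interval, and the descriptive table carries a matching summary;
- the mediation models use the same scale for the same marker.

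If a fuller analysis plan already says this, a reference to it is enough.

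The cost is a short addition to the text and no new data. The small downside is that effects are reported as ratios instead of differences. The timing allows it: section 3 describes the trial as ongoing, section 2.6.3 places biomarker analyses after data collection is complete, and section 2.5 keeps the blind until the analysis is complete. Fixing the scale now also removes a choice that would otherwise be made after the data are seen.
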